##### Regulators of Muscle Fiber Size

The secondary muscle cellular outcomes reflecting the regulators of muscle fiber size are (1) number of myonuclei per muscle fiber, (2) number of satellite cells per muscle fiber, (3) proteins involved in muscle protein degradation (muscle breakdown), and (4) regulators of muscle protein synthesis (local growth factors). Muscle fiber myonuclear and satellite cell content per muscle fiber will be measured by immunohistochemical analysis of the cross-sections of muscle biopsies. Myonuclei and satellite cell contents per muscle fiber will be assessed for the different muscle fiber types separately. Regulators of muscle fiber size, that is, proteins involved in muscle protein synthesis and protein degradation will be measured by western blot analysis in the muscle homogenate. See Table 1 for details.

##### Regulators of Muscle Fiber Function and Cellular Stress

Proteins involved in protection against cellular stress (heat shock protein [Hsp]27, αB-crystallin, Hsp60, and Hsp70) as well as enzymes involved in mitochondrial function (citrate synthase, cytochrome c oxidase subunit 4, and 3-hydroxyacyl-CoA-dehydrogenase) will be assessed in muscle homogenates by western blot analysis. In addition, mitochondrial structures will be studied in cross-sections and whole fiber preparations of muscle biopsies by immunohistochemistry. DNA damage and repair will be assessed using the comet assay [36].

##### Myokines With Potential Antitumor Effects

Exploratory analyses on the effects of the training on the expression levels of myokines, previously proposed to have an antitumor effect, will be conducted. Relevant targets, including, but not limited to, interleukin (IL)-6, IL-15, secreted protein acidic and rich in cysteine, and TNF-related weak inducer of apoptosis will be evaluated at the mRNA level by real-time polymerase chain reaction analyses (RNA extracted from biopsies) and at the protein level by western blot and enzyme-linked immunosorbent assays (muscle and blood samples). Blood samples will be obtained by venipuncture and participants are asked to avoid smoking and alcohol and not to engage in any strenuous physical activity 24 hours before the blood sample collection. The levels of IL-6, IL-8, IL-10, IL-1β, IFN-γ, tumor necrosis factor (TNF)-α, and TNFR1 will be measured using enzyme-linked immunosorbent assay–based methods. Frozen sera will be saved for further analyses that can be included later.

#### Physical Functioning

##### 1RM Testing

1RM testing will be performed as described previously [34] in chest press, leg press, and knee extension. To secure the validity of the 1RM tests, all participants will undertake a familiarization session prior to these assessments.

##### Muscle Endurance

Muscle endurance will be measured as the number of repetitions the patient is able to perform in a continuous set at 30% of 1RM at the corresponding time point in knee extension.

##### Cardiorespiratory Fitness

Cardiorespiratory fitness will be measured as VO_2max_ during maximal walking/running until exhaustion on a treadmill (PPS Med 55, Woodway Inc). The protocols start at 5 km/h with an incline of 5%. The inclination increases with 1% every minute until it reaches 12%, from which the speed increases by 0.5 km/h per minute until exhaustion. Oxygen consumption and minute ventilation will be measured continuously using an oxygen analyzer (Oxycon Pro, Erich Jaeger GmbH; Vyntus CPX, Vyaire Medical GmbH). Heart rate will be measured using a heart rate monitor (T34, Polar Electro KY).

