### Study Design

This study is a 2-group randomized controlled trial (Figure 1). The participants will be randomly allocated into 1 of the 2 training groups: one group performing the combination of strength and endurance training with high intensity and the other group performing the training with low-to-moderate intensity during (neo-)adjuvant treatment for breast cancer. To measure the effect of the treatment itself, a parallel usual care group receiving no supervised training will be recruited from another pool of patients. This will be from patients living too far away from the study site to participate in training and from a usual care control group from another substudy within the Phys-Can consortium carried out at Uppsala University Hospital [31]. The usual care group will have the same inclusion and exclusion (see below) criteria as the 2 training groups in this study. Muscle biopsies, questionnaires, and blood samples will be collected from the training groups before the first chemotherapy cure (T0). The first 2-4 weeks after cure 1 will be used as a familiarization period for tests and exercises and for completing the remaining T0 tests. Testing will include measurements of physical capacity, body composition, and physical activity levels. All measurements, including muscle biopsies, questionnaires, and blood samples, will be repeated halfway into the treatment (T1) and after completion of treatment (T2). In the participants in the usual care group, measurements will be performed at T0 and T2 only. Training will start between cure 2 and cure 3 and will last throughout the treatment period, which is approximately 6 months.

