**Physical function**			
	Muscle strength	1 repetition maximum in chest press and knee extension.	
	Muscular endurance	Repetitions until failure at 30% of 1 repetition maximum	
	Cardiorespiratory fitness	Maximal oxygen uptake	
	Lactate threshold	Blood lactate profile	
Potential antitumor myokines (including, but not limited to interleukin (IL)-6, IL-15, SPARC^m^, TWEAK^n^, IL-8, IL-10, IL-1β, IFN-γ^o^, TNF-α^p^, TNFR1^q^)			mRNA levels by real-time polymerase chain reaction analyses and protein levels by western blot and enzyme-linked immunosorbent assay

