**Quality of life and fatigue**			
	Fatigue	Multidimensional fatigue inventory	
	Pain	Brief pain inventory	
	Health-related quality of life	European Organization for the Research and Treatment of Cancer Quality of Life Questionnaire Core 30, The European Organization for the Research and Treatment of Cancer Quality of Life for breast cancer	
Sociodemographic data (age, partnership, number and age of children living at home, education, income, work and sick leave)			Study-specific questionnaire
Lifestyle data (dietary habits, alcohol consumption, physical activity level, weight, and tobacco use)			Study-specific questionnaire
Behavioral data (motivation, self-efficacy, and barriers to training)			Study-specific questionnaire
Disease-specific information (diagnosis, type, and dose of oncological treatment, adherence to oncological treatment)			Medical records
Adverse events (adverse events occurring during exercise training sessions and during muscle biopsy sampling)			Reported by coaches/technicians

^a^PI3K: phosphoinositol-3-kinase.

^b^Akt: protein kinase B.

^c^mTOR: mechanistic target of rapamycin.

^d^P70s6k: ribosomal protein S6 kinase.

^e^4EBP1: eukaryotic translation initiation factor 4E-binding protein 1.

^f^eIF4A: eukaryotic initiation factor-4A.

^g^FOXO: forkhead box O.

^h^LC3: microtubule-associated protein 1 light chain 3.

^i^p62: ubiquitin-binding protein p62.

^j^CS: citrate synthase.

^k^COX4: cytochrome c oxidase subunit 4.

^l^HADH: 3-hydroxyacyl-CoA-dehydrogenase.

^m^SPARC: secreted protein acidic and rich in cysteine.

^n^TWEAK: TNF-related weak inducer of apoptosis.

^o^IFN-γ: interferon γ.

^p^TNF-α: tumor necrosis factor-α.

^q^TNFR1: tumor necrosis factor receptor 1.

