#### Background Variables

Participants will provide self-reports about age, partnership, number and age of children living at home, education, income, work, sick leave, dietary habits, alcohol consumption, physical activity level, weight, tobacco use, motivation, self-efficacy, and barriers to training by using a study-specific questionnaire. In addition, past illnesses and other medical problems are recorded. Information about the medical situations such as treatment, stage of disease, and comorbidity as well as chemotherapy treatment compliance and adverse events will be collected at all 3 assessment points (T0, T1, and T2) from medical records.

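### The adverse event outcome in Table 1 covers training sessions and biopsies only, so events during the study's own physical tests fall outside it in all three groups

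*Protocol article*

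**What the plan says.** The Outcomes section states that Table 1 lists every outcome. The adverse event row gives the scope as "adverse events occurring during exercise training sessions and during muscle biopsy sampling" and the source as "Reported by coaches/technicians". Several other Table 1 rows (the hypertrophy proteins, the degradation proteins, the myokines) are explicitly open-ended. The adverse event row is not.

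The physical tests are described under Physical Functioning and Blood Lactate Profile:
- VO2max is measured by "maximal walking/running until exhaustion on a treadmill".
- For strength, "1RM testing will be performed as described previously [34] in chest press, leg press, and knee extension".
- Muscle endurance is listed in Table 1 as "Repetitions until failure at 30% of 1 repetition maximum".
- The lactate profile uses bouts at rising submaximal workloads.

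According to Study Design, the training groups are measured at T0, T1 and T2 and the usual care group at T0 and T2 only.

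A second route appears under Background Variables: "chemotherapy treatment compliance and adverse events will be collected at all 3 assessment points (T0, T1, and T2) from medical records".

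**The concern.** The safety outcome names two settings, training and biopsy, and omits a third in which study staff ask the women for hard effort. T1 falls in the middle of chemotherapy, and some T0 tests are completed after the first cycle, so these tests take place during treatment. The Introduction itself raises anthracycline cardiotoxicity and says that the feasibility of high-intensity exercise in all phases of treatment is uncertain. Events under maximal effort therefore bear on the study's subject.

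The gap is also uneven. A training participant can contribute events from training and, if she has biopsies, from biopsy. A usual care participant can contribute biopsy events only, and a usual care participant without a biopsy can contribute none. A table of adverse events by group would then partly reflect which settings were counted. A statement that the study procedures were well tolerated would not cover the tests.

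**Working it through.** The article gives no figure to reproduce. The check sets the passages side by side and then counts the test visits affected.

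**1. Setting by setting**

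| Setting | High intensity | Low-to-moderate | Usual care | In the Table 1 outcome? |
|---|---|---|---|---|
| Training sessions | yes | yes | none supervised | yes |
| Biopsy sampling | those who agree | those who agree | those who agree | yes |
| VO2max, 1RM, muscle endurance, lactate profile | T0, T1, T2 | T0, T1, T2 | T0, T2 | no |

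The only setting shared by every participant is the one left out. In the Abstract, 17 usual care women were enrolled by June 2022, 16 with biopsies. For 17 − 16 = 1 woman, no event caused by the study can enter the outcome.

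**2. Does the medical-record route close the gap?** Background Variables states that "adverse events will be collected at all 3 assessment points (T0, T1, and T2) from medical records". Three features leave the matter open:
- In the full sentence, adverse events follow directly on chemotherapy compliance. They may mean adverse events in general or those of chemotherapy only.
- The source is the hospital record. A strain or dizziness dealt with at the test site need not reach it.
- It refers to three assessment points, whereas usual care has two.

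So the route can catch a test event that reaches the record, but it does not bring test sessions into the outcome.

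**3. Test visits affected.** Inputs from Sample Size: 80 women in the training groups, 20 in usual care. Inputs from Study Design: 3 and 2 visits.
- Planned, assuming full recruitment and attendance: 80 × 3 + 20 × 2 = 240 + 40 = 280.
- At the June 2022 enrolment in the Abstract (38 + 36 = 74 and 17), again with full attendance: 74 × 3 + 17 × 2 = 222 + 34 = 256.
- 1RM tests at 280 visits: 280 × 2 = 560 with the two lifts in Table 1, or 280 × 3 = 840 with the three under 1RM Testing. The two places differ, so only the range can be given.

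Dropouts, for which the sample size allows, would lower all of these.

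**4. What recording would allow.** With zero events in n women, the one-sided upper 95% bound is 1 − 0.05^(1/n), approximately 3/n.
- n = 80 + 20 = 100: 3/100 = 3.0% (exact form 2.95%).
- n = 74 + 17 = 91: 3/91 = 3.3%.

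The woman is the right unit, because two or three tests on the same woman are not independent. Dividing by visits (3/280 = 1.07%) would claim too much precision.

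**The case against.** The strongest reply is that this is a condensed article. Table 1 gives adverse events one row, the full protocol is not shown, and incident recording by test staff is the kind of detail that an article leaves out. That stands to this extent: nothing here shows that test events are not recorded. It does not remove the point, because the article is not silent. It names a closed list of settings in a table said to hold all outcomes, and tests are not on the list.

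A second reply is that the scope is defensible: it covers the randomised intervention and the one invasive procedure, and the tests are the same in both randomised arms. That is fair for the comparison of intensities. It is weaker for a description of harms, and it does not cover usual care, where the training element is empty.

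A third reply is that most women were enrolled by June 2022 and Uppsala data collection was finished, so a change would make early and late ascertainment unequal. This is true. It is a reason to report the limitation, not to keep the narrow scope.

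Some stronger readings are tempting, and the article does not support them:
- **Test harms go uncounted.** The medical-record route may catch some.
- **The hardest efforts all lie outside the outcome.** High-intensity training at 6RM and 10RM load, with Omni ratings of 9-10, is near-maximal and is covered. The lactate profile is submaximal.
- **The tests at T0, T1 and T2 are the only maximal efforts asked of low-to-moderate women.** Strength Training also describes 6RM and 10RM load tests during familiarisation, not limited to one group.
- **A test injury would appear as dropout without a cause.** Nothing says that reasons for withdrawal go unrecorded.

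**Conclusion.** The point holds as one of scope. As worded, the adverse event outcome excludes events during the study's physical tests in all three groups and reduces usual care to biopsy events. The medical-record collection described elsewhere has a different source, an uncertain scope and a visit schedule that does not fit usual care, so the two passages need reconciling.

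The size is about 280 test visits in 100 women at the planned numbers, or 256 visits in 91 women at the June 2022 enrolment, both assuming full attendance. Had test events been recorded and none seen, the study could exclude a per-woman risk above about 3%. Under the present wording it cannot make that statement from its defined outcome.

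The conclusion rests on reading the Table 1 row as a closed list, which the open-ended wording of other rows supports. The full protocol may record more. The point does not affect the primary outcome or the randomised comparison of muscle fibre size. It is worth correcting because it limits what the trial can say about harm and because the remedy is small.

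**What to change.** 1. Reword the Table 1 row to cover adverse events during any study procedure: training sessions, physical tests (VO2max, 1RM, muscle endurance, lactate profile) and muscle biopsy sampling. Apply it to all three groups, with reports from coaches, test staff and technicians.
2. Reconcile this with Background Variables. State whether the medical-record collection covers all adverse events or those of chemotherapy only, and give the assessment points for usual care as T0 and T2.
3. Tabulate events by group and procedure, showing the numbers of women and test visits, because the groups have different numbers of visits.

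The cost is one definition, one clarifying sentence and a line on the test form, with no extra visit or staff. The drawback is that test events before the change can be recovered only from existing test forms and records. Earlier ascertainment will be less complete, notably for the finished Uppsala usual care group, and the report should say so.

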#### Blood Lactate Profile

The patients will walk or run in 5 minutes at bouts with increasing submaximal workloads. Heart rate will be monitored continuously, and capillary blood samples will be taken and analyzed for lactate levels (Lactate Scout+, EKF GmbH) after each workload. The test will terminate when the patients show increased lactate concentrations by more than 1.6 mmol/L from the last workload or when the lactate increases above 4 mmol/L.

#### Body Composition

Total and regional lean body mass and fat mass together with bone mineral density will be measured by dual energy X-ray absorptiometry (iDXA, GE Lunar). Participants will be scanned from head to toe in a supine position, providing values for total and regional lean body mass fat mass, bone mineral content, and bone mineral density.

#### Assessment of Physical Activity Level and Physical Training

Participants’ physical activity level will be measured using SenseWear Armband Mini (BodyMedia Inc). All participants will be instructed to wear the SenseWear Armband for 7 consecutive days. Only valid days with at least 80% wearing time will be included in the analyses. The step count cut points corresponding to moderate intensity will be 3 metabolic equivalents of task [37]. SenseWear Armband data will be analyzed with the SenseWear software (SenseWear Professional Research Software Version 8.1, BodyMedia Inc). Participants will be instructed to keep a logbook of all endurance trainings and strength trainings. In this logbook, the duration and subjective intensity measured with the Borg scale [35] of all endurance training sessions are noted. For the strength training, the load, number of repetitions, number of sets, and the perceived exertion with Omni scale are noted for each session.

#### Quality of Life, Fatigue, and Pain

The European Organization for the Research and Treatment of Cancer Quality of Life Questionnaire Core 30 [38] and diagnosis-specific modules (The European Organization for the Research and Treatment of Cancer Quality of Life for breast cancer) will be used to assess the quality of life. Fatigue will be assessed using the Multidimensional Fatigue Inventory [39], and pain will be assessed using Brief Pain Inventory [40].

#### Background Variables

Participants will provide self-reports about age, partnership, number and age of children living at home, education, income, work, sick leave, dietary habits, alcohol consumption, physical activity level, weight, tobacco use, motivation, self-efficacy, and barriers to training by using a study-specific questionnaire. In addition, past illnesses and other medical problems are recorded. Information about the medical situations such as treatment, stage of disease, and comorbidity as well as chemotherapy treatment compliance and adverse events will be collected at all 3 assessment points (T0, T1, and T2) from medical records.

### Statistical Analyses

Data will be analyzed according to the intention-to-treat principle. Analyses will include standard descriptive statistics, 2-sided *t* tests, correlation, regression, and 2-way repeated-measures analysis of variance or the comparable nonparametric test as necessary to examine the differences between and within groups at T0, T1, and T2. In addition, a per-protocol analysis, that is, adherence to the protocol, will be conducted. Should imbalances in important variables be detected, sensitivity analyses will also be added including these as covariates in the model.

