### Randomization

Participants from Haukeland University Hospital will be randomized in a 1:1 ratio into the 2 training groups stratified by treatment (neoadjuvant or adjuvant treatment). The investigator performing the analyses on muscle biopsies will be blinded for this randomization. As described, participation in the usual care group will be from patients living too far away from the study site at Haukeland University Hospital or from Uppsala University Hospital and will not be randomized.

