## Discussion

The main aim of this study is to compare the effects of a high-intensity strength and endurance training program with those of a low-to-moderate intensity strength and endurance training program on muscle cellular outcomes, muscle function, and cardiorespiratory fitness in women undergoing breast cancer chemotherapy. These results will also be compared with those of the group treated with usual care to investigate how (neo-)adjuvant treatment with chemotherapy will affect these variables and how high and low-to-moderate intensity trainings can counteract the effects of treatment. We hypothesize that the usual care control group will experience negative treatment effects on muscle fiber CSA and mitochondrial function, leading to reduced muscle function and cardiorespiratory fitness. We further expect that both high-intensity training and low-to-moderate intensity training performed by the training groups will counteract the negative treatment effects and that high-intensity training will be superior to low-to-moderate-intensity training. The results of our study are expected to provide insights on how regular exercise during treatment may counteract the side effects of chemotherapy on physical functioning and muscle tissue and how training intensity impacts these effects. Such knowledge can be used to design effective physical exercise programs, helping an increasing number of individuals with breast cancer during and following chemotherapy and possibly reducing the long-lasting side effects and ultimately improve the quality of life.

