Forty women recently diagnosed with breast cancer, with 20 in each group, will give us a larger study population than those in previous studies on muscle cellular outcomes [12,41,42] to draw conclusions from. Furthermore, to our knowledge, this will be the first randomized controlled study comparing the effectiveness between high-intensity strength and endurance training and low-to-moderate intensity strength and endurance training during (neo-)adjuvant treatment on muscle cellular outcomes in patients with breast cancer. We are also recruiting participants who are not willing to undergo muscle biopsies, giving us an even larger study population when analyzing the other outcomes. As high-intensity training is shown to induce larger improvements in maximal oxygen uptake and muscle strength in both healthy individuals and in various patient populations [27,28], it should also be more effective in patients with breast cancer during chemotherapy. However, it is not known to which extent chemotherapy interferes with normal adaptation to physical training, and the high-intensity training is severely more challenging. Consequently, high-intensity training may be less feasible during chemotherapy, and lower adherence to the planned training in some periods of treatment may reduce training effectiveness. However, the feasibility of the current high-intensity training program has been confirmed in the large-scale Phys-Can study [29], in which ~75% of the participants completed the 6-month training program.

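### The three-visit repeated-measures ANOVA does not fit the usual care schedule and, on unimputed data, reduces the randomised intention-to-treat comparison to completers

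*Protocol article*

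**What the plan says.** All of the following is in the protocol article.

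- **Principle (Statistical Analyses):** "Data will be analyzed according to the intention-to-treat principle". A per-protocol analysis based on adherence is added.
- **Methods (same section):** a list of "2-sided *t* tests, correlation, regression, and 2-way repeated-measures analysis of variance". The last item reads in full "2-way repeated-measures analysis of variance or the comparable nonparametric test as necessary". The stated purpose is "to examine the differences between and within groups at T0, T1, and T2". The article does not say which method serves which comparison.
- **Visits (Study Design):** the training groups are measured at T0, T1 and T2. For the others, "In the participants in the usual care group, measurements will be performed at T0 and T2 only". The Abstract says the same.
- **Role of usual care (Discussion):** "These results will also be compared with those of the group treated with usual care". The first two hypotheses in the Introduction also set training against usual care.
- **Allocation (Randomization):** the two training groups are randomised 1:1, stratified by neoadjuvant or adjuvant treatment. Usual care comes from other pools of patients "and will not be randomized".
- **Attrition:** Sample Size sets 20 biopsied women per training group as an allowance for dropouts. The Discussion cites an earlier study of the programme "in which ~75% of the participants completed the 6-month training program".

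**The concern.** A classical group-by-time repeated-measures ANOVA needs a value from each woman at every level of time. That causes two separate difficulties.

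First, the method is named for three visits, but one of the three groups attends only two of them. As described, it cannot hold the usual care group.

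Second, unless missing values are imputed, a trained woman who misses one biopsy or test is removed entirely, including the visits she did attend. The randomised comparison is then between those who stayed in each arm. The article itself allows that the harder programme may prove more difficult to sustain alongside chemotherapy, so the women who stay could differ between the arms. That is the contrast the Discussion calls the main aim. An analysis of completers also moves the intention-to-treat result closer to the per-protocol one, so the two tell the reader less together. Recruiting extra women protects power but does nothing about selection.

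**Working it through.** **1. Visits against method**

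| Group | T0 | T1 | T2 | Usable in a three-visit ANOVA | Usable on T0 and T2 |
|---|---|---|---|---|---|
| High intensity | yes | yes | yes | women with all three visits | women with both |
| Low-to-moderate intensity | yes | yes | yes | women with all three visits | women with both |
| Usual care | yes | none by design | yes | 0 of the 20 planned with biopsies; 0 of the 17 enrolled by June 2022 | women with both |

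The zeros follow from the schedule and need no assumption. The last column shows that the usual care comparison is available by other methods in the same list.

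**2. The article's own sample sizes**

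Inputs from Sample Size: 10 per group for 80% power and 16 per group for 95%. The effect, standard deviation and alpha are not given there. I assume a two-sample t test with two-sided alpha 0.05.

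Power = P(|t| > critical value), where t is noncentral with 2n − 2 degrees of freedom and noncentrality d × √(n/2).

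- Solving for 80% at n = 10 gives d = 1.325 (noncentrality 1.325 × √5 = 2.96).
- At that d, 95% power needs n = 15.8, so 16. Power at n = 16 is 95.2%.

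The two stated figures agree with each other. Other conventions fit slightly less well: the two-sided normal approximation gives 17 (94.3% at 16), and a one-sided t test also gives 17 (93.9% at 16). This shows internal consistency only, because the source effect is not stated.

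**3. Complete cases and power per training arm**

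Complete cases = 20 × (1 − loss). All loss rates are assumptions.

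| Assumed loss | Complete cases of 20 | Power at d = 1.325 |
|---|---|---|
| none | 20 | 98.3% |
| 20% | 20 × 0.80 = 16 | 95.2% |
| 25% | 20 × 0.75 = 15 | 93.8% |
| 30% | 20 × 0.70 = 14 | 92.1% |

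At 25% loss, power falls by 98.3 − 93.8 = 4.5 percentage points.

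**4. Missed visits instead of dropout**

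If T1 and T2 are each missed independently with probability q (assumed), the complete fraction is (1 − q)²:

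- q = 5%: 0.95² = 0.90, or 18.1 of 20
- q = 10%: 0.90² = 0.81, or 16.2 of 20
- q = 15%: 0.85² = 0.72, or 14.5 of 20

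Modest non-attendance at each visit is therefore enough to remove 10% to 28% of women from a three-visit ANOVA. A likelihood-based mixed model keeps whatever each of them contributed.

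**The case against.** The strongest reply is that the ANOVA is one item in a list to be used as needed. It is not declared the primary or only analysis. A t test or baseline-adjusted regression on T0 and T2, or the same ANOVA limited to those visits, would include usual care. This stands. A reader might infer that the comparison with usual care cannot be made at all, and the article does not support that.

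A reader might also take the exclusion of usual care from the ANOVA as a breach of intention-to-treat. It is not one: that group is not randomised, so the principle governs only the two training arms.

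Next, listwise deletion is not written in the article. It follows only if the ANOVA is run without imputation, and a missing-data rule may sit in a fuller plan that is not shown. This stands as a condition on the second difficulty, so an outright contradiction with intention-to-treat is not established. It does not touch the first difficulty, which comes from the visit schedule.

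The figure of about 75% is completion of training in an earlier study. It is not visit or biopsy attendance here, and a woman may stop training and still attend T2. It can serve only as an illustrative loss rate.

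The loss of power is small, as the working shows, and no document gives a figure for the bias. That is correct, and the concern should not be argued on power.

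Finally, a reader might suppose that the nonparametric fallback would lose the between-group comparison. It need not: rank methods for group-by-time designs exist, and a rank test on change scores keeps the contrast. No criticism is made on that ground.

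**Conclusion.** The concern holds in a limited form. It is certain from the article alone that a three-visit repeated-measures ANOVA cannot include usual care, and that the article does not say which listed method makes the usual care comparison. It is conditional on analysing unimputed data that the same ANOVA would restrict the randomised comparison to women with all three visits. That fits poorly with the stated principle in a trial that expects dropouts.

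The harm is possible selection of completers, of unknown size and direction. The cost in power is minor: about 94% with 15 per arm against 98% with 20. Those figures rest on the back-solved effect d = 1.325, a two-sided alpha of 0.05 and an assumed 25% loss.

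**What to change.** In Statistical Analyses, replace the repeated-measures ANOVA for the randomised arms with wording such as:

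> The two training groups will be compared with a linear mixed model for repeated measures, with group, time and group × time, the neoadjuvant/adjuvant stratum, REML estimation and small-sample degrees of freedom. All available T0, T1 and T2 values from all randomised women will be used, in the group to which they were allocated. T0 will be modelled as the first response, with a mean common to both groups. The primary contrast is high minus low-to-moderate intensity at T2.

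Modelling T0 this way adjusts for baseline, so T0 should not also be entered as a covariate.

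Then add a separate statement: each training group will be compared with usual care on T0 and T2 only, by regression of the T2 value adjusted for T0, and reported as a non-randomised comparison.

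**Cost.** A change of wording, standard software and slightly more analysis work; no new data or visits. The mixed model assumes that data are missing at random given what was observed, so it does not protect against dropout that depends on unobserved values. A woman with only a T0 value adds almost nothing to the T2 contrast. The assumption is still weaker than the one a completers-only analysis needs.
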